**In non-CTIMPs, a serious adverse event (SAE) is defined as an untoward occurrence that:**

- (a) results in death;
- (b) is life-threatening;
- (c) requires hospitalisation or prolongation of existing hospitalisation;
- (d) results in persistent or significant disability or incapacity;
- (e) consists of a congenital anomaly or birth defect; or
- (f) is otherwise considered medically significant by the investigator.

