#### 21.2.2 Adverse events reporting parameters

**An SAE occurring to a research participant should be reported to the main REC, where in the opinion of the Chief Investigator (CI) the event was:**

- Related – that is, it resulted from administration of any of the research procedures, and
- Unexpected – that is, the type of event is not listed in the protocol as an expected occurrence.

All SAEs, SARs and SUSARs (excepting those specified in this protocol as not requiring reporting) should be reported immediately to the Chief Investigator and to the Sponsor.

Reports of Serious Adverse Events (SAEs) that are **related** to the study (i.e., they resulted from administration of any of the research procedures) and **unexpected** (i.e., not listed in the protocol as an expected occurrence) should be submitted to the REC using the [Non-CTIMP safety report to REC form](#).

These should be sent within 15 days of the Chief Investigator becoming aware of the event. Reports of SAEs in double-blind trials should be unblinded. There is no requirement for annual safety reports in addition to the information provided through the annual [progress report](#). More detailed description of adverse events reporting parameters is included in Table 3.

Table 3. Adverse events reporting parameters.

|                                                                        | Who                | When                                                                                                                           | How                                                                                                                                                                                                                        | To Whom                                                                                                             |
|------------------------------------------------------------------------|--------------------|--------------------------------------------------------------------------------------------------------------------------------|----------------------------------------------------------------------------------------------------------------------------------------------------------------------------------------------------------------------------|---------------------------------------------------------------------------------------------------------------------|

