The CI will have responsibility for informing the other sites of the SUSAR and any relevant safety information, which may be delegated to the Trial Manager. The CI will also inform the local clinical care team (CAMHS or Community Paediatrics) or GP under which the participant is routinely seen for of any SUSARs (details of which are obtained at screening/referral).

Events categorised in the protocol as an expected (see 20.3), do not need to be reported.

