### **21.3 Expected adverse events**

The following list describes expected adverse events. These events will be reported in the main publication, but not to the REC, unless they meet the serious adverse reaction criteria, in which case they will be reported as described above.

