#### Family dynamics:

- Deterioration in child behaviour (including self-harm) or wellbeing.
- Deterioration in sibling wellbeing (including self-harm).
- Increased family discord.
- Breakdown in family structure.
- Social work involvement or child protection concerns.

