### Adverse Events Form

### Adverse Events Form

This form was completed based on:

1. A report from a research assistant?
2. A completion of an online questionnaire?

| 1. Details of adverse event
(describe below what has been reported)

[free text up to 500 characters] | 2. Medical/physical health
1. Cardiovascular
2. Respiratory
3. Hepatic
4. Gastro-intestinal
5. Genito-urinary/renal
6. Endocrine
7. Haematological
8. Musculo-skeletal
9. Neoplasia
10. Neurological
11. Psychological
12. Immunological
13. Dermatological
14. Allergies
15. Eyes, ear, nose, throat | 3. Mental health/behaviour

0. No
1. Yes | 4. Relationships or daily activities difficulties

0. No
1. Yes | 5. Start date | 6. Outcome
1. Resolved
2. Resolved with treatment/intervention
3. Ongoing | 7. End date | 8. Relationship to intervention
1. Definitely related
2. Likely
3. Possibly
4. Unlikely
5. Not related | 9. Expected?
1. Expected
2. Unexpected | 10. Is this event serious?
0. No
1. Results in death
2. Is life-threatening
3. Requires hospitalisation or prolongation of existing hospitalisation
4. Persistent or significant disability or incapacity
5. Consists of a congenital anomaly or birth defect | 11. SUSAR?
0. No
1. Yes | 12. Who is involved?
1. Target child
2. Target parent | 13. Has the event led to the family no longer participating in the study?
0. No
1. Yes |

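### The safety sections conflict on whether a related serious event on the expected list is reported to the REC, and the adverse event forms do not match the SAE definition

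*Protocol*

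**What the plan says.** **Text of 21.2.2.** An SAE goes to the REC if it is related and unexpected, where unexpected means that "the type of event is not listed in the protocol as an expected occurrence". All SAEs, SARs and SUSARs go at once to the Chief Investigator and Sponsor, except those that the protocol says need no reporting. After Table 3, a 24-hour notice to the Chief Investigator is tied to events meeting the SUSAR definition.

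**Table 3, SAE row.** The Chief Investigator sends SAEs to the main REC within 15 days, copied to the sponsor. The row has no condition on relatedness or expectedness.

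**Last sentence of 21.2.2.** "Events categorised in the protocol as an expected (see 20.3), do not need to be reported".

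**Section 21.3.** "These events will be reported in the main publication, but not to the REC, unless they meet the serious adverse reaction criteria", and then "in which case they will be reported as described above". The list that follows includes "Deterioration in child behaviour (including self-harm) or wellbeing".

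**Definitions and forms.** The last SAE criterion in 21.2.1, (f), covers an event that "is otherwise considered medically significant by the investigator". The seriousness codes in item 10 of the Adverse Events Form (Appendix 4) stop at "5. Consists of a congenital anomaly or birth defect". In the parent questionnaire on medical and psychological events (Appendix 3, MAPED), the No branch of question 5 points to question 4.

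**The concern.** A member of staff handling a serious event that is judged related to STEPS, and whose type is on the expected list, cannot follow all of these passages. Depending on which is read first, the event goes to the REC within 15 days or does not go at all. The closing sentence of 21.2.2 can also be taken as the exemption that the Chief Investigator and Sponsor rule leaves open, which would remove that notice too.

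The list is not limited to trivial events. It names self-harm in the child, without a limit on severity, and child protection concerns, in a trial of an unguided app for families of children aged 5 to 11. At stake are prompt independent oversight of related serious events and the completeness of the harms data. The two form defects add a smaller risk: an event serious only under criterion (f) may be filed as not serious, and some parents may be misrouted in the questionnaire.

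**Working it through.** No sample size, rate or test enters this point, so the check sets the passages side by side.

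**Test event.** Child self-harm leading to hospitalisation, judged related to STEPS. It is serious (hospitalisation is an SAE criterion in 21.2.1), related by assumption, and its type is on the list in 21.3.

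| Rule | Condition | Result for the test event |
|---|---|---|
| 21.2.2 text, REC | related and type not listed | second condition fails: not to REC |
| 21.2.2 Table 3, SAE row | SAE | to REC within 15 days |
| 21.2.2 last sentence | listed as expected | no reporting |
| 21.3 opening | listed, but a serious reaction | reported, by the route in 21.2.2 |
| 21.2.2 text, Chief Investigator and Sponsor | any SAE not exempted elsewhere | yes, unless the last sentence of 21.2.2 is the exemption; then no |
| 21.2.2 text, 24-hour notice | meets SUSAR definition | not triggered, since a SUSAR must be unlisted |
| 21.1, database | any adverse event | recorded, and SAEs followed to resolution |
| 21.2.2, DMC | serious adverse reaction or SUSAR | told at its regular meetings (about six-monthly, 20.2) |
| 21.3, publication | listed event | reported |

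The first four rows give no, yes, no and yes in intent. Whether the exception in 21.3 works depends on what its back-reference means. If it means the text rule, the event is turned away because it is listed. If it means Table 3, it has a route.

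**Cross-reference.** Section 20 contains only 20.1 and 20.2. The expected events are in 21.3.

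**Size of the list.** School and community 2, family dynamics 5, parent wellbeing 4: 2 + 5 + 4 = 11 items.

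**Seriousness codes.** SAE criteria (a) to (f) make 6. Item 10 offers 0 for No and codes 1 to 5, which match (a) to (e). So 6 − 5 = 1 criterion, (f), has no code.

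**MAPED skips on No.** Question 1 leads to 2, 2 to 3, 3 to 4, 4 to 5, 5 back to 4, 6 to 7, and 7 to 8. Only question 5 goes backwards. Built literally, that branch does not reach questions 6 to 8, including question 7 on concerns about taking part.

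**The case against.** The strongest reply is that the conflict is one of wording and that other routes stay open. The closing sentence of 21.2.2 does little more than point to the expected-events section, which opens with the serious-reaction exception, so it can be read as shorthand for it. Table 3 gives that exception a possible route. Immediate notice of SAEs to the Chief Investigator and Sponsor is already required, which is stricter than 24 hours. The database, SAE follow-up, DMC and publication provisions all still apply.

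Most of this stands, and it limits the point. Three stronger readings are tempting but not supported:

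- A reader might infer that such an event is not reported at all. The database, DMC and publication provisions rule that out.
- A reader might infer that the exception in 21.3 is empty. It is empty against the text rule, but Table 3 offers a route.
- A reader might infer that the SUSAR route can hardly ever operate. Self-harm is listed for the child and siblings, not the parent, and 21.2.1 defines an unexpected reaction partly by severity, so an unusually severe episode could be argued to be unexpected.

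The reply does not make the passages agree. The SUSAR definition and the REC rule both turn on whether the event is listed, not on severity. Table 3 is introduced as further detail on the same rules, so its SAE row may be only an abbreviation of the text condition. Immediate notice to the Chief Investigator and Sponsor is subject to an exemption that the closing sentence can be taken to supply.

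On the forms, a criterion (f) event can be described in the 500-character free text of item 1, and the MAPED skip is probably a slip that the live form may not share.

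**Conclusion.** The point holds as an internal contradiction with a bounded consequence. For a related serious event whose type is among the 11 listed, prompt REC notice could be missed and, on one reading, Chief Investigator and Sponsor notice as well. The event would still be recorded, made known to the DMC as a serious reaction, and published.

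The form gap is exact but narrow. An event serious only under criterion (f), one of six criteria, can be described but not coded as serious. If it is then filed as not serious, it could also miss the DMC route. The MAPED skip is a minor error, and questions 5 and 6 carry no hospitalisation probe, so it should not be read as preventing SAEs from being recorded.

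No treatment estimate or test changes. The conclusion assumes that the forms are built as printed, and that the box which 21.2.2 mentions for the SUSAR definition, not present in the text available, adds no further rule. The documents do not show that every related SAE must go to the REC whatever its type, or that the 24-hour notice must apply to all serious events. Those would be policy choices beyond reconciling the text.

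**What to change.** 1. Reconcile the text rules of 21.2.2, the SAE row of Table 3, the last sentence of 21.2.2 and the opening of 21.3 into one stated rule for related serious events on the expected list. The serious-reaction exception in 21.3 should have a working route, and the last sentence of 21.2.2 should no longer override it.
2. Correct the reference from 20.3 to 21.3.
3. Make the 24-hour notice consistent with the requirement elsewhere in 21.2.2 for immediate notice of SAEs to the Chief Investigator.
4. Add a code for criterion (f) to item 10 of the Adverse Events Form.
5. Route No at MAPED question 5 to question 6, and check the live electronic form.

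The cost is a protocol wording amendment and two form edits. The downside is a few more safety reports.

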### **21.3 Expected adverse events**

The following list describes expected adverse events. These events will be reported in the main publication, but not to the REC, unless they meet the serious adverse reaction criteria, in which case they will be reported as described above.

#### School/community:

- Increased child refusal to go to school/community activities.
- Exclusion from school/community activities.

#### Family dynamics:

- Deterioration in child behaviour (including self-harm) or wellbeing.
- Deterioration in sibling wellbeing (including self-harm).
- Increased family discord.
- Breakdown in family structure.
- Social work involvement or child protection concerns.

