## 21. Harms

### 21.1 *Specification, Timing and Recording of Safety Parameters*

Please see section 21.2 below for adverse event definitions and reporting parameters. The risk of participants experiencing any adverse events during this trial as a result of using STEPS is very low. Adverse events concerning parental or child physical and mental health will be monitored throughout the trial. Any physical or mental health difficulties spontaneously disclosed by a parent in their communication with researchers will be entered into the Red Pill database using the OPTIMA adverse events form created specifically for the study (see Appendix 4). Moreover, at each timepoint, participants will be asked to complete a formal questionnaire on adverse events (Medical and psychological events and difficulties questionnaire) that happened to them and their child. This information will be collected online using ePRO. The forms will be reviewed regularly, and all adverse events will be recorded on the OPTIMA adverse events form in the Red Pill database. All participants that experience a serious adverse event will be followed-up by the researchers, who have completed Level 2 safeguarding training, until the event is resolved. Where necessary, the participant's clinical service which accepted the referral will be informed about the event.

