### 21.2 *Procedures for Recording and Reporting Adverse Events*

#### 21.2.1 Definitions of adverse events.

**Adverse Event (AE):** Any untoward medical occurrence in a subject to whom a therapy has been administered including occurrences which are not necessarily caused by or related to that therapy.

**Adverse Reaction (AR):** Any untoward and unintended response in a subject to a therapy which is related to any duration of therapy administered to that subject.

**Unexpected Adverse Reaction (UAR):** An adverse reaction the nature and severity of which is not consistent with the information known about the therapy in question in the view of the investigator

**Suspected Unexpected Serious Adverse Reactions (SUSAR):** Any serious adverse events that is deemed to be related to the trial intervention and unexpected (not listed in the protocol as an expected side effect of the intervention).

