### Medical and psychological events and difficulties questionnaire

We want to keep track of whether there are any potential concerns about taking part in OPTIMA. These questions will ask about any **physical** and **mental health difficulties your child** and **you** may have experienced in the last **3 months**. We will also ask about any difficulties **your child** and **you** may have had with daily activities.

This section will ask about any **physical health** or **medical** problems. We will first ask about **your child** and then ask about **you**.

1. Has **your child** had any **physical health** or **medical** problems in the last 3 months?

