**NO: go to Q5**

**YES:**

- Please say a bit more about the problem [500 characters]
- When did this problem start? Please provide approximate date.
- When did this problem end? Please provide approximate day or select 'ongoing' if not resolved.
- Did this problem result in hospitalisation? **Yes/No**. If yes, please describe [500 characters].

This section will ask about any **difficulties in relationships with family members you live with or daily activities**. We will first ask about **your child** and then ask about **you**.

5. Has your child had any **difficulties in relationships with family members you live with or daily activities** at home, school, including online schooling or things that they normally do in the last 3 months?

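### Section 21.3 lists sibling deterioration among the events to be published, but the questionnaire does not ask about siblings and the adverse events form has no code for one

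*Protocol*

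**What the plan says.** Section 21.3 sets out the expected adverse events under three headings. The family dynamics group has separate entries for the referred child and for a sibling, the latter being "Deterioration in sibling wellbeing (including self-harm"). Of the whole list the section says "These events will be reported in the main publication, but not to the REC", with an exception for serious adverse reactions.

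The rest of the safety text is about the parent and the referred child. Section 21.1 states the scope: "Adverse events concerning parental or child physical and mental health will be monitored throughout the trial". Section 21.2.1 defines an adverse event as "Any untoward medical occurrence in a subject to whom a therapy has been administered". Section 10.3.9 describes MAPED as a retrospective report on the parent and their child. In Appendix 3, each of the three topic sections opens by saying "We will first ask about your child and then ask about you".

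The adverse events form in Appendix 4 identifies the person in one field: "12. Who is involved? 1. Target child 2. Target parent". Field 1 of the same form is a free-text description of up to 500 characters.

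Section 21.1 also provides a route that does not depend on the questionnaire: "Any physical or mental health difficulties spontaneously disclosed by a parent in their communication with researchers will be entered into the Red Pill database".

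**The concern.** The list in 21.3 treats a sibling as a distinct person who may be harmed and names self-harm as part of that harm. The section then says the listed events will appear in the main publication. The two instruments that would supply the data were written for two people only, the referred child and the participating parent.

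This has two consequences. The first is ascertainment: parents are asked directly about themselves and the referred child at every assessment, but never about another child in the home. Sibling events would be gathered less completely than most others on the list, and a reader of the harms table could not see this. The second is attribution: a sibling event that does reach the database has no correct value in field 12, so a tabulation by person would show it under the referred child, under the parent, or nowhere.

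**Working it through.** The protocol states no figure on this point, so the check consists of counting and of setting the printed parts side by side.

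**Items listed in 21.3.** School/community 2 + family dynamics 5 + parent wellbeing 4 = 11. One of the 11 names a person who is neither the referred child nor the parent: the sibling item.

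**MAPED questions (Appendix 3).**
- Questions 1, 3 and 5 (physical health; mental health or behaviour; relationships and daily activities) are about the child.
- Questions 2, 4 and 6 cover the same three topics for the parent.
- Question 7 asks whether the difficulties described raised concerns about taking part. Question 8 asks about good things that happened because of taking part.
- Questions on a sibling's wellbeing: 0 of 8.

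The nearest approach is in questions 5 and 6, which refer to "difficulties in relationships with family members you live with or daily activities". There a sibling can appear only as the other party in a difficulty that the child or parent is having. A parent might mention a sibling's state in the free text, but the question does not ask for it.

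**Adverse events form (Appendix 4).**
- Field 12 codes that identify a sibling: 0 of 2. Field 13 follows intact, so no third code appears to have been lost from the text.
- Field 9 asks whether the event was expected. Under 21.3 a sibling event can be marked as expected there, while field 12 on the same row cannot say whose event it was.
- Field 1 can name the sibling in words.

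**Path of a sibling event.**
1. It is not asked about, so it enters only by spontaneous disclosure to a researcher (21.1) or through volunteered text at question 5 or 6.
2. If it enters, field 12 must be coded to the referred child or the parent, or left blank. The protocol does not say whether a blank is allowed.
3. The correct person can be recovered by reading field 1. Events that were never volunteered cannot be recovered.

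**The case against.** The strongest reply is that 21.3 is mainly a list of what counts as expected, so that such events need not go to the ethics committee. Publishing whatever was recorded would satisfy its wording. That is right. A reader might infer that the protocol promises to ask about siblings or to give a sibling event rate, but it promises neither.

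A reader might also infer that sibling events cannot be recorded at all. The documents do not support that. The spontaneous-disclosure sentence in 21.1 is not limited to the parent and referred child, questions 5 and 6 allow free text about the household, and field 1 can hold the description.

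Siblings are not participants, and asking about them systematically would mean collecting information on a child outside the trial. That is a fair reason not to add a question. It does not explain why an event on the protocol's own list cannot be coded to the person concerned. Siblings are also foreseeable here: section 10.3.3 already asks whether other children with neurodevelopmental difficulties live in the household.

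Finally, the sibling item differs from some others only in degree. Family breakdown and social work involvement have no MAPED question of their own, and field 12 has no family code. This stands, but those events involve the child's or parent's own household life, which questions 5 and 6 do address. A sibling's self-harm is not covered in that way.

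**Conclusion.** The mismatch is real and minor. One of the 11 listed events concerns a person covered by 0 of the 8 MAPED questions and 0 of the 2 codes in field 12. Sibling events are recorded only if volunteered, and a recorded one can be attributed correctly only from free text.

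Some under-counting is to be expected, but the protocol gives neither a sibling event rate nor a volunteering rate, so no size is offered. It would be going too far to say that the published harms data will mislead. That would require a sibling count printed without saying how it was obtained, which the protocol does not prescribe.

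The conclusion assumes that the electronic forms match the printed appendices. It is confined to harms reporting: no primary, secondary or economic analysis is affected, nor is any progression criterion.

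**What to change.** Add a third code to field 12 for a sibling or other child in the household. Read the field 1 text of events already recorded and recode any that concern a sibling. When reporting harms, state that sibling events were not solicited, so that a low count is not evidence of no harm. The cost is one form code, a small recoding task and one sentence.

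A MAPED item on other children in the home is optional. It would lengthen the form slightly, collect information on a child who is not a participant, need ethics review, and yield data only from the date of the change.

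Separately, the printed instruction after a negative answer to MAPED question 5 sends the parent back to question 4, where a negative answer leads to question 5 again. This is a misprint for question 6. It should be corrected and the online routing checked, but the point above does not depend on it.
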